### 3.4.2 Eligibility criteria

People who meet **all** of the inclusion criteria and **none** of the exclusion criteria are eligible to enter this study.

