- g) heart rate < 50 beats per minute on pre-entry electrocardiogram and participant is symptomatic.
11. Taking regular medications that may prolong the PR or QRS interval durations, such as any of the antiarrhythmic medications Class I [fast sodium (Na) channel blockers (e.g. quinidine, disopyramide, procainamide, lidocaine, phenytoin, flecainide, propafenone)].
  12. Unable to swallow oral tablets.
  13. Severe gastrointestinal disease (including oesophagitis, gastritis, malabsorption).
  14. History of a gastrectomy.
  15. Recent history of radiotherapy of oesophagus area.
  16. Diabetes mellitus with secondary organ dysfunction (coronary heart disease, previous stroke, renal insufficiency), or poorly controlled diabetes (patients with glycosylated haemoglobin – HbA1c >7% or hyperglycaemia – measured as a fasting blood glucose >7mmol/L or a random blood glucose >11mmol/L) despite receiving clinic-based diabetes care.
  17. Diagnosis of anorexia caused by other reasons, as determined by the investigator such as:
    - a) advanced AIDS;
    - b) heart failure;
    - c) uncontrolled thyroid disease.
  18. Receiving strong CYP3A4 inhibitors (including clarithromycin, erythromycin, diltiazem, itraconazole, ketoconazole, ritonavir, verapamil, etc.) within 14 days of randomization.
  19. Currently receiving tube feedings or parenteral nutrition (either total or partial).
  20. Current use of excessive alcohol or illicit drugs.
  21. Any condition, including the presence of laboratory abnormalities, which in the Investigator's opinion, places the potential participant at unacceptable risk if he/she were to participate in the study or confounds the ability to interpret study data.
  22. Enrolment in a previous study with anamorelin HCl or previous exposure to anamorelin HCl.
  23. Actively receiving a concurrent investigational agent or having received an investigational agent within 28 days of Day 1.
  24. Cognitive impairment (Short Blessed Test (SBT) score  $\geq 10$ ).

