**Vital signs** including body temperature (°C), blood pressure (mmHG, systolic and diastolic), respiratory rate (breaths per minute) and heart rate (beats per minute) will be measured as part of the safety assessments at every visit: screening (Visit 1) and at Weeks 4, 8 and 12 (Visits 3, 4 and 5) as well as during optional extension phase at Weeks 18 and 24 (Visits 6 and 7). Pulse rate, systolic and diastolic blood pressure will be measured after the patient has been resting in the semi-supine position for at least 5 minutes.

A **complete medical history** will be recorded at the screening visit (Visit 1) and will include evaluations for past or present conditions. **Concomitant medications** will also be recorded at every visit: screening (Visit 1), baseline (Visit 2) and at Weeks 4, 8 and 12 (Visits 3, 4 and 5) as well as during optional extension phase at Weeks 18 and 24 (Visits 6 and 7).

**12-lead ECGs** will be conducted at screening (Visit1), Weeks 4, 8 and 12 (Visits 3, 4 and 5). Any new or worsening ECG abnormalities assessed to be clinically significant by the study investigator will be reported as adverse events. When possible, ECG will be recorded at 1 hour ( $\pm 5$  minutes) post dose to align with occurrence of Cmax. At screening visit ECG will be taken pre-dose (as no dose will be administered at this time).

**Short Blessed Test** will be administered at screening to assess cognitive capacity and will assist the PI to assess eligibility by determining the persons capacity to understand the study and to complete the assessments. A score of 10 or more is required.

**Adverse event assessment** the research team member who sees the participants and their caregivers will also ask about any other unexpected adverse outcomes. The study investigators will oversee the research team members. All serious adverse events will be reported in accordance with the requirements of the approving central Research and Ethics Committee as defined in the committee's safety reporting standard operating procedures (see section 9.1 Adverse Events). Serious adverse events will be followed until documentation of resolution or the successful initiation of relevant management strategies. Other adverse events will be described in the Annual Report to the Committee.

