## 7.0 PARTICIPANT TIMELINE

### 7.1 Visit 1 (Screening)

If the Investigator considers a person to be potentially eligible for the study, written informed consent for participation in the study must be obtained prior to any study-related procedures. The following procedures will be performed, and data collected during this visit for eligibility purposes:

| Clinician                                                                                                                                                                              | Patient-reported outcomes        |
|----------------------------------------------------------------------------------------------------------------------------------------------------------------------------------------|----------------------------------|
| Informed consent                                                                                                                                                                       | FAACT A/CS (score of $\leq 37$ ) |
| Demographic and Clinical information (including on the tumour, staging of disease, planned treatment and treatment undertaken to date, etc.)                                           |                                  |
| Medical history                                                                                                                                                                        |                                  |
| Prior and concomitant medication                                                                                                                                                       |                                  |
| Complete and dedicated physical examination                                                                                                                                            |                                  |
| Vital signs                                                                                                                                                                            |                                  |
| Short Blessed Test (SBT score $\geq 10$ )                                                                                                                                              |                                  |

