| AKPS Performance Scale (score $\geq 50$ )                                                                                                                                              |                                  |
| 12-Lead ECG                                                                                                                                                                            |                                  |
| Laboratory blood tests* including random glucose ( $\leq 11$ mmol/L), HbA 1c ( $\leq 7\%$ ), AST and ALT ( $\leq 5 \times$ ULN), and renal function (CrCl $> 20$ mL/minute) |                                  |
| Urine pregnancy test for females of childbearing potential                                                                                                                             |                                  |
| Provide participant diary and pedometer – instruct to complete step count and 3-day food diary and bring to baseline visit                                                             |                                  |
| Caregiver: Informed consent                                                                                                                                                            |                                  |

\* Ensuring that the study involves minimal burden to participants is crucial in this study, therefore, in some instances (e.g., if clinical picture has not otherwise changed), blood samples taken as part of diagnosis as well as pre-chemo/radiation therapy can be used for screening.

Based on the relevant above mentioned assessments outcome, the Investigator will decide if the person is eligible for the study. If eligible, they will be given the study diary and pedometer (if applicable) to complete the 3-day food diary and step count and bring it to baseline visit (Visit 2). The study nurse will book DEXA scans at screening visit for participant to have it done as part of baseline assessment.

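### The protocol contradicts itself on the Short Blessed Test cut-off: exclusion criterion 24 bars a score of 10 or more, while section 6.2 requires it and the Visit 1 table lists it as if it qualified

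*Supplement*

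**What the plan says.** The current protocol (V1.6, 7 April 2022) gives the SBT eligibility rule in three places.

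- **Section 3.4.2.2, exclusion criterion 24.** The criterion opens "Cognitive impairment (Short Blessed Test (SBT) score" and sets the cut-off at 10 or above. Section 3.4.2 makes this binding: people who meet all of the inclusion criteria and none "of the exclusion criteria are eligible to enter this study".
- **Section 6.2, Short Blessed Test.** The test is given at screening and "will assist the PI to assess eligibility by determining the persons capacity to understand the study and to complete the assessments". The next sentence reads "A score of 10 or more is required".
- **Section 7.1, Visit 1 table.** The clinician column has the entry "Short Blessed Test (SBT score $\geq 10", with no note on whether this value admits or excludes.

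Table 6-1 schedules the SBT once, at screening. The protocol does not describe how the test is scored. No footnote reconciles the three places, and no entry in the amendment listing (section 13.0) mentions the SBT cut-off.

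**The concern.** One cut-off is used in opposite directions for the same test, visit and purpose. The two places that describe the conduct of the screening visit (6.2 in words, 7.1 by its layout) point the opposite way from the formal criterion.

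The stake is who enters the trial. Section 6.2 presents the test as a check that a person can understand the study and complete its assessments. Requiring a score that criterion 24 calls impairment defeats that aim. The trial also leans on what participants report: the FAACT anorexia items behind the first efficacy endpoint and the SQUASH are self-completed (section 6.7), and outpatients take the drug unsupervised at home and record it in a diary (section 11.3.4). An error in the other direction, turning away people who score below 10, would also distort the recruitment rate, which is one of the five feasibility criteria in section 5.1.1.

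**Working it through.** No sample-size or error-rate arithmetic is involved. The check compares the set of scores that each place admits.

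| Place | Statement | Scores that can enter |
|---|---|---|
| 3.4.2.2, criterion 24 | 10 or more is cognitive impairment and excludes | below 10 |
| 6.2 | 10 or more is required | 10 or more |
| 7.1, Visit 1 table | 10 or more, direction not stated | 10 or more, if read like its neighbours |

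**Step 1: can both rules hold?** Someone who satisfies 6.2 scores 10 or more. Someone who satisfies criterion 24 scores below 10. The sets are complements and their intersection is empty, so nobody is eligible if both are applied.

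**Step 2: is the 7.1 entry a pass value or a flag for exclusion?** Read alone it could be either. The other thresholds in that table are:

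| Item in 7.1 | Value shown | Matching criterion | Role in 7.1 |
|---|---|---|---|
| FAACT A/CS | 37 or less | inclusion 4 | qualifies |
| AKPS | 50 or more | inclusion 5 | qualifies |
| AST and ALT | up to 5 x ULN | inclusion 6 | qualifies |
| Creatinine clearance | above 20 mL/minute | inclusion 7 | qualifies |
| Random glucose | 11 mmol/L or less | exclusion 16 (above 11) | qualifies; sign turned round |
| HbA1c | 7% or less | exclusion 16 (above 7%) | qualifies; sign turned round |
| SBT | 10 or more | exclusion 24 (10 or more) | sign **not** turned round |

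All six other thresholds are pass values. The two taken from an exclusion criterion were turned round when they were entered. The SBT, the third taken from an exclusion criterion, was not. A reader who treats the table consistently would take 10 or more as a pass, and 6.2 says so outright.

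**Step 3: could this be a damaged symbol?** No. Section 6.2 gives the rule in words.

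**Step 4: which direction do the documents support?** Only criterion 24 attaches a meaning to a score, by labelling 10 or more as cognitive impairment. Sections 6.2 and 7.1 give a number without saying what it signifies. On the protocol's own text, then, a higher score means worse cognition, and 6.2 and 7.1 are the likelier slips. That inference rests on a single line.

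**Step 5: what would follow at a site?** If 6.2 or 7.1 alone were followed and nothing later intervened, every person admitted would meet exclusion criterion 24 and every person scoring below 10 would be refused. This restates Step 1 and does not forecast enrolment. The documents give no distribution of SBT scores, so the number affected among the planned 50 cannot be estimated.

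**The case against.** A reader might infer that sites will enrol cognitively impaired people. The documents do not support that. The numbered criteria are the formal rule, and several later checks run against them: the site investigator reviews the completed eligibility screening and approves randomisation (8.4), the inclusion and exclusion criteria are checked again at Visit 2 (7.2), the coordinating centre monitors eligibility and cross-references it with randomisation (4.3, 8.4), and monitoring covers eligibility (9.2.3). Reasons for non-entry are logged (8.4), so a site refusing everyone who scored below 10 would probably be noticed. The eligibility worksheet that sites complete is not shown, and whether it carries the wrong threshold is unknown.

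A reader might also infer that the validity of consent hangs on this screen. It does not. Section 7.1 requires written consent before any study procedure, so consent precedes the SBT. Ability to consent and comply is separately required by inclusion criterion 9 and addressed in the consent discussion (8.2). Section 6.2 describes the SBT as an aid to the investigator.

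Nor do the adherence measures rest wholly on participants' own records. Drug adherence can fall back on a count of remaining tablets (4.7) and diet on a recall collected by the nurse (6.7), although a recall still depends on the participant's account.

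These objections stand as limits on the consequence. They do not remove the contradiction, and the safeguards are incomplete. The SBT is not repeated at Visit 2, and a person wrongly refused at Visit 1 never reaches the re-check. The eCRF applies range checks (9.4.3), so a threshold copied from 6.2 could be built into the database.

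**Conclusion.** The contradiction is certain and is an internal inconsistency, not a choice of design. Criterion 24 and section 6.2 cannot both be met, and the Visit 1 table sides with 6.2 when read like the rest of that table. The consequence is conditional: people whom the protocol defines as impaired would enter, and others would be turned away, only if a site worked from 6.2 or 7.1 and the later checks missed criterion 24. No count or probability can be attached to that.

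The conclusion that 6.2 and 7.1 are the places in error assumes that the label in criterion 24 correctly describes the direction of the scale. The documents offer nothing else to confirm it.

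This must be fixed because an eligibility rule stated in two opposite ways cannot be applied as written and the repair is small. It does not rest on an expectation that mis-enrolment will occur.

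**What to change.** 1. Reconcile criterion 24, section 6.2 and the Visit 1 table in 7.1. First confirm the direction of the score against the instrument's scoring key. If the key agrees with the label in criterion 24, reword 6.2 and 7.1 so that a score below 10 is needed to enter and 10 or more excludes, and add a line to 6.2 saying what a high score means.
2. Put the same rule in the eligibility worksheet and in the eCRF validation check.
3. Review the SBT values of everyone already screened, both those randomised and those recorded as not entered because of the SBT.

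The cost is two lines in a protocol amendment, one eCRF check and a short review of values already held. It adds no visit, test or burden for participants.

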**Anamorelin for anorexia, V1.6, 07 April 2022**

### ***Clinical Global Impression (CGI)***

The CGI is a two-item clinician-rated questionnaire designed to assess impression of disease severity (CGI-S) and global improvement or change (CGI-i) with a seven-point scale (1-7) - 1 = "Normal or not ill" 2 = "Borderline ill," 3 = "Mildly ill," 4 = "Moderately ill" 5 = "Markedly ill," 6 = "Severely ill," or 7 = "Among the most extremely affected subjects"; and 1 = "Very much improved" 2 = "Much improved," 3 = "Minimally improved," 4 = "No change" 5 = "Minimally worse," 6 = "Much worse" or 7 = "Very much worse", respectively." CGI-S will be filled out at baseline (Visit 2) and Weeks 4, 8 and 12 (Visits 3, 4 and 5) and at Week 24 during the optional extension phase (Visit 7). CGI-i will be filled out at Weeks 4, 8, 12 (Visits 3, 4 and 5) and at Week 24 (Visit 7) if applicable.

## **6.3 Comorbidity assessment**

Comorbid conditions will be recorded using the Charlson Comorbidity Index which incorporates in a single score the severity and number of comorbid conditions . The index is an independent predictor of long-term survival (predicting the 10-year survival in patients with multiple comorbidities), and although long-term mortality may not be the most important factor in this study, it allows a uniform measure of comorbidity in a population where this may be frequently encountered. The Charlson Comorbidity Index will be used without weighting.

## **6.4 Demographics**

1. Age and date of birth
2. Biological gender
3. Postcode
4. Language spoken at birth and at home
5. Ethnicity, including Aboriginal or Torres Strait Islander status
6. Smoking history/ smoking status
7. Country of birth

## 6.5 Main clinical diagnosis

Relevant information on tumour type, staging (limited vs. extensive), date of diagnosis, sites of metastasis and cancer treatment received and planned (including when available, relevant eVIQ protocol number) will be collected at the screening (Visit 1). The extent of disease will be recorded as limited or extensive for the purposes of stratification.

Small cell lung cancer treatment regimen and any dose or interval adjustments will also be collected at relevant follow up visits during cancer treatment, including baseline and Weeks 4, 8 and 12 (Visits 2, 3, 4 and 5), and 18 and 24 (Visits 6 and 7, if extension phase). In addition, response to therapy for target lesions of SCLC will be collected at Weeks 12 (Visit 5) and 24 (Visit 7, if extension phase).

## 6.6 Functional status

### ***Australia - modified Karnofsky Performance Status***

The Australia-modified Karnofsky Performance Status (AKPS) is a validated variant of the Karnofsky Performance Status scale. The Australian version has criteria that can be applied in either the inpatient or outpatient setting and reflects the greater emphasis on community-based care. This objective measure has high inter-rater reliability and is sensitive to changes in function over time. A score of 0 to 100 (in increments of 10) is assigned to participants based on their ability to undertake a range of daily tasks. The score gives an indication of the participant condition (in terms of physical ability) and can assist in prognostication. The tool will be used in this study to assist investigators to determine participant condition and possible prognosis, together with any measurable improvements in functional status as a result of the intervention. The AKPS will be collected at every visit: screening (Visit 1), baseline (Visit 2), and at Weeks 4, 8 and 12 (Visits 2, 3, 4 and 5) as well as during optional extension phase at Weeks 18 and 24 (Visits 6 and 7).

### ***Step count***

A downloadable pedometer app (*stepapp* – available for free) will be used to objectively track physical activity (step count) of patients during the study. The mobile app should be used at all times over 2 days (preferably one weekday and one weekend day) immediately prior to visits during baseline, Weeks 4, 8 and 12, and at Weeks 18 and 24 for the optional extension. Participants who do not have mobiles, will be given a wearable digital pedometer. Participants will be asked to enter daily step count on a diary. Differences in absolute and percentage change for these data will be analysed.

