**Secondary - Clinical assessment (proposed for any subsequent phase III study)**

- Baseline demographic and clinical predictors of responders.
- Body weight, BMI and historical stable weight.
- Lean body mass (measured by change in dual x-ray absorptiometry (DEXA) and Bioelectrical Impedance Analysis – BIA) and muscle mass at T4 (measured by computed tomography -CT scan) by arm.
- Functional status using clinician-rated Australia-modified Karnofsky Performance Scale (AKPS).
- Timed up and go test (TUG).
- Dynamic function as measured by a pedometer app or a wearable digital pedometer, for participants who do not have mobiles, worn for two days prior to visits.
- Nutritional intake measured by self-reported 3-day food diary, including 2 weekdays and one weekend day prior to visits. If participants do not complete the 3-day food diary prior to visits, a 24-h diet recall will be collected by the study nurse at the time of visit.
- Biochemical changes (including IL-6, CRP, albumin and pre-albumin).

- Survival (overall and cancer-specific).
- Participant rated global impression of change (GIC).
- Clinician rated clinical global impression of severity and improvement (CGI-S, CGI-i)
- Quality of life assessed with EQ-5D-5L – EuroQoL five-dimensional instrument, and ICECAP-A – ICEpop CAPability measure for Adults.
- Participant-reported fatigue as measured by the Functional Assessment of Chronic Illness Therapy-Fatigue (FACIT-F) domain.
- Unplanned health care contacts including hospitalisations.
- Episodes of febrile neutropaenia.
- Adverse events from chemotherapy (e.g., nausea, vomiting, anorexia, fatigue).
- Harms in each arm.

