## **5.2 Secondary endpoints**

### **5.2.1 Secondary efficacy (clinical assessments proposed for any subsequent phase III study)**

1. Baseline demographic and clinical predictors of responders.
2. Change in body weight and BMI at every visit and assessment of historical stable weight at baseline.
3. Change in lean body mass measured at baseline and week 12 (or 24) by dual x-ray absorptiometry (DEXA) and Bioelectrical Impedance Analysis (BIA).
4. Change in muscle mass at thoracic (T4) level, measured by electronically stored data from computed tomography (CT) scans whenever they are done clinically.
5. Functional status using clinician-rated Australia-modified Karnofsky Performance Scale (AKPS) measured as area under the curve from data collected at every scheduled visit.
6. Timed *up and go test* (TUG) measured at every scheduled visit.
7. Functional performance as measured by a pedometer app (stepapp) or a wearable digital pedometer, for participants who do not have mobiles, worn for two days (preferably one weekday and one weekend day) prior to visits.
8. Nutritional intake measured by self-reported 3-day food diary, including 2 weekdays and one weekend day prior to visits. If participants do not complete the 3-day food diary prior to visits, a 24-h diet recall will be collected by the study nurse at the time of visit.
9. Biochemical changes including C Reactive Protein (CRP), IL-6, albumin and pre-albumin from baseline.
10. Survival (overall and cancer-specific) measured with data of death from the time of enrolment.
11. Changes overtime in the participant rated Global Impression of Change (GIC) and in the clinician rated Clinical Global Impression of Severity and Improvement (CGI-S, CGI-i).
12. Changes overtime in quality of life measured by EQ-5D-5L (EuroQoL five-dimensional instrument) and ICECAP-A (ICEpop CAPability measure for Adults).

13. Changes overtime in participant-reported fatigue as measured by the Functional Assessment of Chronic Illness Therapy-Fatigue (FACIT-F) domain.
14. Rates of unplanned hospitalisations (defined as an emergency admission; or unplanned emergency contact with GP, nurses, specialists, home help visit, etc.; or unplanned readmission within 28 days following discharge to the same facility – participant may arrive at hospital in own transport or in an ambulance) and length of stay; with primary reasons kept in a diary by participants.

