## 10.0 STATISTICS

### 10.1 Power and sample size

A total of 50 participants with small cell lung cancer will be randomised 1:1 to anamorelin HCl 100 mg or placebo in order to have data at 12 weeks on 40 participants (approximately 20 in each treatment arm). Since this is a feasibility study, it is not required to calculate a fully justified sample size for establishing the efficacy of the intervention. It has been suggested, however, that in feasibility studies, a sample size between 24 and 50 is acceptable. The findings from this study will be used to inform the calculation of a sample size for a future larger scale phase III trial.

Participants discontinued after randomisation will not be replaced.

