### **Efficacy outcomes**

Changes from baseline to 12 weeks or 24 weeks in each of the secondary endpoints will be calculated. An exploratory analysis of the potential differences between arms will be performed using t-test for continuous normally distributed data or Wilcoxon Test for continuous non-normally distributed data.

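### Mean percentage change in step count is inflated within each arm and undefined at zero baseline; a baseline-adjusted log analysis and a wider recording window would mend this at little cost (low priority)

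*Supplement*

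**What the plan says.** Section 6.6 (Step count) names two metrics and makes neither the main one: "Differences in absolute and percentage change for these data will be analysed".

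Section 10.3 (Efficacy outcomes) sets out the general analysis: "Changes from baseline to 12 weeks or 24 weeks in each of the secondary endpoints will be calculated", and then "An exploratory analysis of the potential differences between arms will be performed using t-test for continuous normally distributed data or Wilcoxon Test" when the data are continuous but not normal. Neither test adjusts for the baseline value. Section 10.4 adds that descriptive summaries of every outcome measure will be used to decide which measures suit a definitive trial.

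The recording window is worded in three ways:

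- Section 6.6: "The mobile app should be used at all times over 2 days (preferably one weekday and one weekend day) immediately prior to visits".
- Section 5.2.1, item 7 (the endpoint definition): "worn for two days (preferably one weekday and one weekend day) prior to visits", without *immediately*.
- Trial Summary: "worn for two days prior to visits", with no day mix.

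No section gives a step-count SD or CV, a rule for a zero baseline, or a fixed weekday for visits.

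**The concern.** Percentage change divides by a baseline built from only two days. A person whose baseline days happened to be quiet shows a large gain, a person whose days happened to be busy shows a smaller loss, and the two do not cancel. The mean therefore exceeds zero even if nobody has changed, and people with very low baseline counts dominate it. Such people are plausible here: section 3.4.2.1 admits a performance status down to 50, and section 11.3.4 allows for inpatients. A zero baseline leaves percentage change undefined, and section 10.3 allows no imputation.

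At stake is the judgement this trial is meant to inform, namely whether step count suits phase III and how large and variable its change is. A mean gain made of measurement noise, with a large SD attached, is a poor basis for that.

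The window raises a separate question. Two consecutive days just before the visit often cannot include one weekday and one weekend day. If a participant's visits fall on different weekdays, the mix of days can differ between visits.

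**Working it through.** **No planned figure to reproduce.** The protocol states no effect size, variability or power for step count. The only related number is in section 10.1: 50 are randomised "in order to have data at 12 weeks on 40 participants (approximately 20 in each treatment arm"), and 40 / (1 − 0.20) = 50. So 20 per arm is used below. Every CV is an assumption.

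**1. Mean percentage change when nothing has changed.** Let X (baseline) and Y (follow-up) be two-day means with the same true level and independent lognormal within-person error of CV c. With σ² = ln(1 + c²), ln(Y/X) has mean 0 and variance 2σ². Then:

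- E[Y/X] − 1 = exp(σ²) − 1 = c²
- SD[Y/X] = (1 + c²) × √((1 + c²)² − 1)
- median of Y/X = 1, so median percentage change is 0

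| CV of two-day mean (assumed) | Mean percentage change |
|---|---|
| 10% | 1% |
| 20% | 4% |
| 30% | 9% |
| 40% | 16% |
| 50% | 25% |
| 60% | 36% |

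At CV 30%, 40% and 50% the SD is 47, 68 and 94 percentage points. With 20 per arm the standard error is SD/√20, about 10.5, 15.2 and 21.0 points, so the inflation is roughly one standard error.

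The range depends on which CV is meant. If days are independent, a two-day-mean CV of 30% to 50% corresponds to a single-day CV of about 42% to 70% (0.42/√2 = 0.30; 0.70/√2 = 0.49), with simulated inflation of 8.7% and 23.8%. If 30% to 50% is instead the single-day CV, the inflation is about 4% to 12%.

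**2. Between-arm comparison with no effect.** Simulation with 20 per arm, mean 4000 steps and between-person CV 0.6 (both assumed):

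- CV 30%: mean percentage change 9.0% in each arm, difference 0.0 points.
- CV 50%: 24.8% and 24.7%, difference −0.1 points.
- Type I error of the t-test on percentage change: 4.8% in both cases.
- Mean absolute change: −2 to −3 steps, that is, no inflation.

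**3. Power, 20 per arm, two-sided 5%, true log effect 0.4 (ratio about 1.5).** The adjusted analysis also depends on the between-person spread; a CV of 0.6 gives these figures to within about one point.

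| CV of two-day mean | t-test, % change | Wilcoxon, % change | Log steps adjusted for baseline |
|---|---|---|---|
| 40% | 56% | 60% | 69% |
| 50% | 39% | 42% | 54% |

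**4. The two calendar days immediately before each visit day.**

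- Monday: Saturday and Sunday
- Tuesday: Sunday and Monday (mix met)
- Wednesday: Monday and Tuesday
- Thursday: Tuesday and Wednesday
- Friday: Wednesday and Thursday

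Only Tuesday, 1 of 5 weekday visit days, gives one weekday and one weekend day.

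**The case against.** Four stronger readings are tempting, and the protocol supports none of them.

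- *Step count is analysed only as percentage change.* The same sentence also plans absolute change, which does not have this inflation.
- *The inflation could produce a false treatment effect.* It is equal in both arms, and the between-arm test keeps its error rate.
- *Skewed data would be forced through a t-test.* Section 10.3 sends non-normal data to the Wilcoxon test. Percentage change is a monotone function of the log ratio, so that test gives the same p-value on either scale, and ranks stop a few near-immobile people from dominating it.
- *The day-mix rule is breached on four weekdays out of five.* The mix is only preferred, and the endpoint definition in section 5.2.1 omits *immediately*, so a site following that section can obtain the mix for any visit day. A changing mix within a person also requires visits to move between weekdays, which the protocol neither states nor prevents.

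The stakes are also limited. Step count is one of 17 secondary items, its testing is exploratory, and no progression criterion in section 5.1.1 uses it: adherence to physical activity advice rests on the SQUASH questionnaire.

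All of this stands, and it sets the priority low. It leaves four things untouched. The Wilcoxon test protects the test but not the reported mean and SD. The zero-baseline case has no rule. Neither metric is named as the main one. Neither planned test uses the baseline as a covariate.

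**Conclusion.** The point holds in a limited form. Mean percentage change is inflated within each arm by about c², and the direction is the same for any within-person variability under the lognormal model. Its size cannot be fixed from the protocol. A reader might take 9% to 25% as the expected inflation, but that range requires an assumed two-day-mean CV of 30% to 50%.

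The damage is to the descriptive summaries used under section 10.4, not to the validity of the comparison between arms. The power given up is modest: against the Wilcoxon test, about 9 points at CV 40% (69 − 60) and 12 points at CV 50% (54 − 42), under the assumptions in the working.

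The window finding is an awkward fit between *immediately* and the preferred mix in section 6.6, plus a difference in wording from section 5.2.1. It is not a breach of any requirement. Because the endpoint is secondary and exploratory, this is a low-priority improvement.

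**What to change.** 1. In section 6.6, replace percentage change with an analysis of log follow-up steps, log(steps + 1), with log baseline steps on the same scale as covariate, back-transformed to a percentage difference between arms. Name this as the main step-count analysis and keep absolute change as supportive.
2. In sections 6.6 and 5.2.1 alike, ask for one weekday and one weekend day within the 7 days before the visit, and use this wording at every visit.

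The cost is one analysis sentence and one line of diary instruction, with no added recording days and no new data. The food-diary text in section 6.7 already uses a looser timing, so the window change fits existing practice. There are two small downsides. A recorded day may be up to 7 days before the visit. And while log(steps + 1) keeps zeros defined, a zero lies far from the rest (ln 1 = 0 against ln 4001 = 8.3), so the number of zeros should be reported and true zeros separated from days when the device was not used.
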